### Primary outcome

The primary outcome will be the proportion of responders at week 5. The proportion of responders at week 8 and week 16 will be assessed as secondary outcome. Participants will be defined as “responders” if showing at least 1 of the 3 following criteria: (1) at least a 50% decrease and absolute change from baseline ≥ 20 in visual analog scale (VAS) score on average pain intensity; (2) at least a 50% decrease and absolute change from baseline ≥ 20 in Australian Canadian Osteoarthritis Hand Index (AUSCAN); (3) at least a 20% decrease and absolute change from baseline ≥ 10 in at least two measurements of VAS score, AUSCAN and patient global assessment of improvement. The responder criteria are summarized by the Outcome Measures in Rheumatological Clinical Trials and Osteoarthritis Research Society International (OMERACT-OARSI) [24]. Responders are acknowledged to have clinically active treatment effect [25], since this assessment uses both a relative and an absolute change in three different domains (pain, function and patient’s global assessment) instead of single measurement.

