### Secondary outcomes

Secondary outcomes will include VAS score on pain intensity, AUSCAN, Functional Index for hand OA (FIHOA), the number of painful joints, tender joints and swollen joints, hand grip strength and pinch strength, global assessment, the World Health Organization Quality of Life abbreviated version (WHOQOL-BREF) and the participants' expectations for acupuncture. As shown in Table 2, the outcome measurements will be assessed at baseline, week 5, week 8, and week 16 after randomization. A responsible research assistant will be assigned by each hospital to complete all outcome assessments during this trial. The research assistants will be blinded from group allocation.

**Table 2 Tab2:** Primary and Secondary Outcomes

Primary outcome	*Overall responder*	
	Showing 1 of the 3 followings: ≥ 50% decrease and absolute change ≥ 20 in VAS score on average pain intensity; ≥ 50% decrease and absolute change ≥ 20 in AUSCAN; ≥ 20% decrease and absolute change ≥ 10 in at least two measurements of VAS score on average pain intensity, AUSCAN and global assessment	Week 5
Secondary outcomes	*Overall responder*	
	Showing 1 of the 3 followings: ≥ 50% decrease and absolute change ≥ 20 in VAS score on average pain intensity; ≥ 50% decrease and absolute change ≥ 20 in AUSCAN; ≥ 20% decrease and absolute change ≥ 10 in at least two measurements of VAS score on average pain intensity, AUSCAN and global assessment	Week 8, week 16
	*Pain*	
	Change in VAS score from baseline on average pain intensity Change in VAS score from baseline on maximal pain intensity The proportion of participants with an at least 15-point decrease in VAS score from baseline on average pain intensity	Week 5, week 8, week 16
	*Physical function*	
	Change in AUSCAN total score from baseline Change in AUSCAN subscale scores including pain, stiffness and physical function from baseline Change in FIHOA from baseline	Week 5, week 8, week 16
	*Patient global assessment*	
	Change in patient global assessment of improvement from baseline	Week 5, week 8, week 16
	*Joint activity*	
	Change in the number of painful joints from baseline Change in the number of tender joints from baseline Change in the number of swollen joints from baseline	Week 5, week 8, week 16
	*Hand strength*	
	Change in hand grip strength from baseline Change in hand pinch strength from baseline	Week 5, week 8, week 16
	*Quality of life*	
	Change in WHOQOL-BREF from baseline	Week 5, week 8, week 16
	*Other outcomes*	

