### Visual analog scale (VAS) for pain intensity

The VAS is a validated scale presented as a 100-mm line on paper, anchored by “no pain” at 0 and “worst imaginable pain” at 100. The participants will be asked to mark the line to estimate pain intensity of their dominant hand during the last 48 h. The VAS score will be measured from 0 to the participant’s mark, with a maximum score of 100 [26]. VAS scores can be categorized into four degrees: 0 (no pain), 1–34 (mild), 35–74 (moderate) and 75–100 (severe) [27]. A 15-point decrease from baseline is required to achieve Minimal Clinically Important Difference (MCID) for patients with hand OA [28]. The change in VAS score from baseline on average pain intensity and maximum pain intensity and the proportion of participants achieved MCID on average pain intensity will be measured at baseline, week 5, week 8, and week 16.

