### Australian Canadian Osteoarthritis Hand Index (AUSCAN)

The AUSCAN index is designed as a self-administered questionnaire for the evaluation of both pain and physical function in hand OA. VAS scaling is presented to the participants for the measurement of pain intensity (during 5 types of activity), stiffness (in the morning), and physical function (during 9 types of activity) [29]. By presenting as a 100-mm line, verbal descriptor “no pain/no stiffness/no difficulty” is anchored on 0 mm and “the most imaginable pain/ the most imaginable stiffness/ the most imaginable difficulty” is anchored on 100 mm for the 3 dimensions. The AUSCAN subscale scores will be calculated as the average of scores within each dimension. Higher scores indicate worse condition [30]. The AUSCAN total score will be the average of scores on the 15 items above. It is a reliable and responsive self-reported measurement that eliminates observer variation. Participant will be asked to complete the AUSCAN to indicate the condition of the dominant hand during the previous 48 h at baseline, week 5, week 8, and week 16.

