### Patient global assessment

The participants’ assessment of their global status of the dominant hands during the last 48 h will be measured using a VAS (0 represents “worst possible”, 100 represents “best possible”) [34] at baseline, week 5, week 8, and week 16. Patient global assessment has been recommended as a core outcome domain of clinical trials in hand OA.

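### Criterion 3 of the primary responder rule counts a fall in patient global assessment as improvement, although that scale runs from 0 (worst) to 100 (best)

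*Protocol article*

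**What the plan says.** The Primary outcome section makes a participant a responder if any one of three criteria is met. Criteria 1 and 2 use pain VAS alone and AUSCAN alone (a fall of at least 50% and 20 points). Criterion 3 is "at least a 20% decrease and absolute change from baseline ≥ 10 in at least two measurements of VAS score, AUSCAN and patient global assessment"; its list of measures reads in full "in at least two measurements of VAS score, AUSCAN and patient global assessment of improvement". Table 2 repeats it for the week 5 primary outcome and again for weeks 8 and 16: "≥ 20% decrease and absolute change ≥ 10 in at least two measurements of VAS score on average pain intensity, AUSCAN and global assessment".

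The three measures are defined separately:

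- Pain VAS is "anchored by “no pain” at 0 and “worst imaginable pain” at 100".
- For AUSCAN, "Higher scores indicate worse condition".
- The patient global assessment "will be measured using a VAS (0 represents “worst possible”, 100 represents “best possible".

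The global item is called an assessment of improvement in the Primary outcome section and Table 2. The Patient global assessment section describes a rating of the global status of the dominant hand over the last 48 hours.

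**The concern.** One direction is applied to three scales that do not share it. For pain VAS and AUSCAN a decrease is improvement; for the global item it is deterioration. The article nowhere says that the global score is reversed or that an increase counts.

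At stake is the classification behind the single primary endpoint and the same endpoint at weeks 8 and 16. Read literally, the global domain stops working as a route to genuine response and can complete a response for someone whose global status has worsened. The Primary outcome section justifies the rule by its use of three domains (pain, function, patient's global assessment), and the literal rule defeats that purpose in one of them.

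**Working it through.** **The plan's own figure.** Inputs from the Sample size section: 83.3% v 69%, two-sided alpha 5%, power 80%, 1:1 allocation, 20% dropout. With unpooled variance,

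n = (1.96 + 0.842)² × [0.833 × 0.167 + 0.69 × 0.31] / (0.833 − 0.69)² = 7.85 × 0.3530 / 0.02045 ≈ 135.5, so 136 per arm; 136 / 0.8 = 170.

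The stated 170 per arm reproduces. It depends only on the two assumed rates, so the direction error does not alter it arithmetically.

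**Two illustrative patients under criterion 3.** Neither meets criterion 1 or 2, because pain falls by only 25% and AUSCAN by 10% or less.

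| | Pain VAS | AUSCAN | Global (0 worst, 100 best) | As written | Global item aligned |
|---|---|---|---|---|---|
| A | 60 to 45: −25%, −15, counts | 50 to 45: −10%, −5, does not count | 40 to 60, better | 1 of 3: non-responder | 2 of 3: responder |
| B | 60 to 45: −25%, −15, counts | unchanged, does not count | 60 to 40, worse: −33%, −20 | 2 of 3: responder | 1 of 3: non-responder |

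Both aligned results hold whichever way the item is aligned. For A, the rise is 20/40 = 50% on the recorded scale, or a fall of 20/60 = 33% on 100 minus the score; both exceed 20% and 10 points.

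**Boundaries of the error.** A patient whose global score falls from 60 to 40 with pain and AUSCAN unchanged scores 1 of 3 and is a non-responder either way. A patient with pain 60 to 45 and AUSCAN 60 to 45 scores 2 of 3 without the global item and is a responder either way.

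**Size, from simulation.** The documents give no baseline means, SDs or correlations, so these are assumptions: baseline means of 60 (pain), 50 (AUSCAN) and 45 (global); SD of change 18–26; correlation between changes 0.4–0.6. Mean improvement was set so that the aligned rule gives 83.3% and 69%. Across these scenarios the literal rule:

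- removes responder status from about 7–12% of participants per arm;
- grants it wrongly to about 0.5–3%;
- lowers the response rate by about 6–11 points per arm;
- gives power of about 74–81% with 136 evaluable per arm, against the planned 80%.

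One scenario (SD 22, correlation 0.6): aligned 83.4% v 69.0%, a difference of 14.4 points; literal 76.7% v 61.0%, a difference of 15.7 points. Status is lost by 7.4% and 9.3%, and wrongly gained by 0.6% and 1.2%.

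**Do the two possible corrections differ?** From baseline b, an increase rule needs max(10, 0.2b) points; a decrease in 100 minus the score needs max(10, 0.2(100 − b)).

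| Baseline | Increase on recorded scale | Decrease on reversed scale |
|---|---|---|
| 20 | 10 | 16 |
| 40 | 10 | 12 |
| 70 | 14 | 10 |

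The first is unattainable above about 83 (100/1.2), the second above 90. In simulation they classify about 98.5–99.4% of participants identically.

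**The case against.** The strongest reply is that this is a drafting slip with an obvious intention. The rule is presented as identifying a clinically active treatment effect, the item is labelled as improvement, and the wording was probably carried over from the two scales on which higher is worse. The analysis plan and derivation code are not shown and may already handle it. That is plausible, and nothing here shows that the data will be scored wrongly. But the article states both the rule and the scale, and they conflict; this is not a detail left to another document. The phrase about absolute change could be direction-neutral, but the 20% decrease cannot. The label does not rescue it either, since a fall on an improvement scale would also be unfavourable.

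The other objections concern reach, and they stand:

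- A reader might infer that patients who worsen become responders and patients who improve do not. That is true of the global item only. It is one of three measures in one of three criteria, and two of the three are needed.
- A reader might infer that replacing decrease by increase would not be enough, because 20% of a baseline of 20 is only 4 points. The 10-point floor applies as well, so 10 points are required.
- A reader might infer that the comparison is biased or the trial badly underpowered. No bias towards either arm is shown, and the modelled power stays close to plan.

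**Conclusion.** The point holds, within limits. The primary responder rule is wrong as written for the global item in criterion 3 at weeks 5, 8 and 16, and should be corrected because it defines the primary endpoint. The contradiction rests on the text alone. The harm is mainly misclassification and a response rate that does not mean what it claims; the effect on power is modest.

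The sizes given (about 7–12% losing status, about 0.5–3% gaining it, response about 6–11 points lower, power about 74–81%) depend on the assumed baselines, SDs and correlations and on literal coding. It would go too far to say that the sample size rests on a different endpoint: the Sample size section does not say how the pilot responses were scored, so this is something to confirm.

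**What to change.** In the Primary outcome section and both responder rows of Table 2, state before unblinding that the global item counts when it improves. One form: score it as 100 minus the recorded value and require a decrease of at least 20% and at least 10 points, with the reversed baseline as denominator. An increase of at least 20% and at least 10 points on the recorded scale is an acceptable alternative and classifies almost everyone the same way; what matters is that one version and its denominator are fixed in advance.

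Name the item consistently as global status, and confirm that the pilot rates of 83.3% and 69% were scored in the same direction.

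Do not change the scale anchors: enrolment was planned from April 2022 and the article appeared in February 2023, so data may already have been recorded on the present scale.

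The cost is one sentence, one line of derivation code and a check of the pilot scoring. No new data are needed and the sample size does not change.

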### Secondary outcomes

Secondary outcomes will include VAS score on pain intensity, AUSCAN, Functional Index for hand OA (FIHOA), the number of painful joints, tender joints and swollen joints, hand grip strength and pinch strength, global assessment, the World Health Organization Quality of Life abbreviated version (WHOQOL-BREF) and the participants' expectations for acupuncture. As shown in Table 2, the outcome measurements will be assessed at baseline, week 5, week 8, and week 16 after randomization. A responsible research assistant will be assigned by each hospital to complete all outcome assessments during this trial. The research assistants will be blinded from group allocation.

**Table 2 Tab2:** Primary and Secondary Outcomes

Primary outcome	*Overall responder*	
	Showing 1 of the 3 followings: ≥ 50% decrease and absolute change ≥ 20 in VAS score on average pain intensity; ≥ 50% decrease and absolute change ≥ 20 in AUSCAN; ≥ 20% decrease and absolute change ≥ 10 in at least two measurements of VAS score on average pain intensity, AUSCAN and global assessment	Week 5
Secondary outcomes	*Overall responder*	
	Showing 1 of the 3 followings: ≥ 50% decrease and absolute change ≥ 20 in VAS score on average pain intensity; ≥ 50% decrease and absolute change ≥ 20 in AUSCAN; ≥ 20% decrease and absolute change ≥ 10 in at least two measurements of VAS score on average pain intensity, AUSCAN and global assessment	Week 8, week 16
	*Pain*	
	Change in VAS score from baseline on average pain intensity Change in VAS score from baseline on maximal pain intensity The proportion of participants with an at least 15-point decrease in VAS score from baseline on average pain intensity	Week 5, week 8, week 16
	*Physical function*	
	Change in AUSCAN total score from baseline Change in AUSCAN subscale scores including pain, stiffness and physical function from baseline Change in FIHOA from baseline	Week 5, week 8, week 16
	*Patient global assessment*	
	Change in patient global assessment of improvement from baseline	Week 5, week 8, week 16
	*Joint activity*	
	Change in the number of painful joints from baseline Change in the number of tender joints from baseline Change in the number of swollen joints from baseline	Week 5, week 8, week 16
	*Hand strength*	
	Change in hand grip strength from baseline Change in hand pinch strength from baseline	Week 5, week 8, week 16
	*Quality of life*	
	Change in WHOQOL-BREF from baseline	Week 5, week 8, week 16
	*Other outcomes*	
	Participants' expectations for acupuncture at baseline Blinding assessment right after the last session Safety assessment during the trial Proportion of participants taking rescue medication Frequency and total dosage of rescue medication	

### Visual analog scale (VAS) for pain intensity

The VAS is a validated scale presented as a 100-mm line on paper, anchored by “no pain” at 0 and “worst imaginable pain” at 100. The participants will be asked to mark the line to estimate pain intensity of their dominant hand during the last 48 h. The VAS score will be measured from 0 to the participant’s mark, with a maximum score of 100 [26]. VAS scores can be categorized into four degrees: 0 (no pain), 1–34 (mild), 35–74 (moderate) and 75–100 (severe) [27]. A 15-point decrease from baseline is required to achieve Minimal Clinically Important Difference (MCID) for patients with hand OA [28]. The change in VAS score from baseline on average pain intensity and maximum pain intensity and the proportion of participants achieved MCID on average pain intensity will be measured at baseline, week 5, week 8, and week 16.

### Australian Canadian Osteoarthritis Hand Index (AUSCAN)

The AUSCAN index is designed as a self-administered questionnaire for the evaluation of both pain and physical function in hand OA. VAS scaling is presented to the participants for the measurement of pain intensity (during 5 types of activity), stiffness (in the morning), and physical function (during 9 types of activity) [29]. By presenting as a 100-mm line, verbal descriptor “no pain/no stiffness/no difficulty” is anchored on 0 mm and “the most imaginable pain/ the most imaginable stiffness/ the most imaginable difficulty” is anchored on 100 mm for the 3 dimensions. The AUSCAN subscale scores will be calculated as the average of scores within each dimension. Higher scores indicate worse condition [30]. The AUSCAN total score will be the average of scores on the 15 items above. It is a reliable and responsive self-reported measurement that eliminates observer variation. Participant will be asked to complete the AUSCAN to indicate the condition of the dominant hand during the previous 48 h at baseline, week 5, week 8, and week 16.

### Functional index for hand OA (FIHOA)

The FIHOA is an investigator-administered questionnaire developed by Dreiser [31], containing 10 questions to assess the functional impact of hand OA. Each question is scored with a four-point Likert scale ranging from 0 to 3. The total score is the sum of all questions (ranging from 0 to 30), with a higher score indicating more severe functional impairment [31]. The FIHOA index has shown internal validity and good consistency with high sensitivity to change [32]. Its association with pain, muscle strength, and EuroQol-5 dimension (EQ-5D) has also been identified [33]. The FIHOA will be performed for the dominant hand only at baseline, week 5, week 8, and week 16.

### Patient global assessment

The participants’ assessment of their global status of the dominant hands during the last 48 h will be measured using a VAS (0 represents “worst possible”, 100 represents “best possible”) [34] at baseline, week 5, week 8, and week 16. Patient global assessment has been recommended as a core outcome domain of clinical trials in hand OA.

### Joint activity

Painful joints, tender joints, and swollen joints of the dominant hand will be counted at baseline, week 5, week 8, and week 16, which will provide information on the number and distribution of symptomatic joints and evaluate joint activity. A total of 15 joints of the dominant hand will be assessed, including the PIP, DIP, metacarpophalangeal (MCP), first interphalangeal (IPJ), and first CMC joints.

### World Health Organization Quality of Life abbreviated version (WHOQOL-BREF)

The WHOQOL-BREF is a frequently used questionnaire to evaluate quality of life. It consists of four domains comprising 26 items: physical (7 items), psychological (6 items), social (3 items), environmental (8 items), and general (2 items) [35]. Each item is scored with an ordinal scale from 1 to 5, with higher scores indicating better quality of life. The raw score of each domain will be the sum of all items and will be transformed to a 0–100 scale according to the formula reported in the WHOQOL-BREF guidelines. The translated simplified-Chinese version of WHOQOL-BREF has been shown to have validity and reliability [36]. The questionnaire will be conducted at baseline, week 5, week 8, and week 16.

### Hand strength

Grip and pinch strength of the dominant hand will be assessed at baseline, week 5, week 8, and week 16. A series of tests including grip, palmar (three-jaw chuck) pinch, key (lateral) pinch, and tip (two-point) pinch have been demonstrated highly reliable for evaluating hand strength [37]. Hand grip strength will be quantified in kilograms by measuring the amount of static force a participant can squeeze around the hand dynamometer (KYTO 2324, Kangdu Electronic Manufacture Co. Ltd, Dongguan, China). Pinch strength will be measured using a Jamar digital pinch gauge (Allegro Medical, Illinois, USA), which will be placed between the radial side of index finger and thumb, between the pulp of the thumb and the index and middle fingers, and between the tip of the thumb and the index finger, respectively, to perform 3 different pinch tests. Participants are supposed to stand with their shoulders slightly adducted and neutrally rotated, and their elbows slightly extended for each of the 4 tests [38]. The mean of three trials (with intervals of at least 30 s) for each test will be calculated and documented as final score.

### Expectations for acupuncture

At baseline, the following question will be elicited to evaluate the participants’ expectations for acupuncture: “What level of improvement do you expect from acupuncture for your hand OA?” Participants can choose one of the alternative answers including “no improvement”, “slight improvement”, “moderate improvement”, “extreme improvement”, and “unclear”.

### Safety assessment

Any acupuncture-associated adverse event (AE), such as dizziness, palpitations, local hematomas, or infection, and any other AE irrelevant to acupuncture, will be carefully observed by the acupuncturist and documented on the adverse event sheet. Serious AEs (such as fatal or life-threatening, disabling, resulting in hospitalization) will be informed to the Medical Ethics Committee of Guang’anmen Hospital within 24 h. After each session, the researchers will document AEs if happens. The trial will be immediately suspended in case of serious AEs.

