**Methods:**

This will be a sham-controlled, randomized, multi-center clinical trial. A total of 340 participants will be recruited and randomly allocated to either traditional acupuncture group or sham acupuncture group. All participants will receive 12 treatment sessions over 4 weeks and 2 follow-up assessments in the following 3 months at week 8 and week 16. The primary outcome will be the proportion of responders at week 5. Secondary outcomes will include visual analog scale, Australian Canadian Osteoarthritis Hand Index, Functional Index for hand OA, the number of symptomatic joints, hand grip strength and pinch strength, global assessment, the World Health Organization Quality of Life abbreviated version and expectations. Safety will be evaluated during the whole process of the trial. All outcomes will be analyzed following the intention-to-treat principle.

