### Randomization and allocation

Eligible participants will be randomly assigned in a 1:1 ratio to either the traditional acupuncture group (TA) or the sham acupuncture group (SA). The randomization scheme will be generated by an independent institute, Lnkmed Tech Co. Ltd. (Beijing, China), and the allocation will be performed and concealed through the Interactive Web Response System (IWRS). Stratified permuted block randomization with center-based stratification and variable block size will be applied by Lnkmed using the SAS version 9.4. IWRS will assign a code to each enrolled participant, which will be concealed from participants, outcome assessors and the statisticians. The acupuncturist will be the only one who have access to both the code and the treatment labeled with the code.

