### Blinding

In this study, the participants, outcome assessors, and the statisticians will be blinded to the group allocation. The acupuncturists will not be blinded due to the characteristics of acupuncture. Sham acupuncture treatment will mimic the similar sensation of traditional acupuncture treatment using blunt-tip needles. To ensure the success of blinding, the acupuncturists will be discouraged from discussing the treatments or expected results with participants. A blinding assessment will be taken right after the participant’s last session that asks the participant to guess which treatment he/she has received.

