### Data management and quality control

The initial data will be filled in case report forms (CRFs) by the responsible outcome assessor and immediately entered into the Electronic Data Capture (EDC) system provided by Lnkmed. The clinical research associates (CRAs) will conduct monitoring activities through the website every week to enhance the quality of trial. The CRFs will be required from the clinical sites when they accomplish all the recruitment, treatment, and assessment of participants. All data on the EDC system will be locked after confirmations are presented by two independent CRAs that data online are consistent with data in the CRFs. Any deviation from the study protocol will be reported in time.

Researchers in all clinical sites will be jointly trained by the principal investigator before we carry out the trial. Acupuncture treatments will be performed by licensed acupuncturists with at least 2 years of experience in clinical practice. Both TA and SA are safe for participants in our trial; thus, no intervention modification is permissible. Considering the management of AEs will be the same in either TA group or SA group and the trial will be suspended for all serious AEs, there will be no unblinding during the trial. Group allocation will be kept by Lnkmed and revealed after the completion of statistical analysis. Participants in the SA group will receive 12 sessions of supplementary TA treatment if they want. Withdrawals or dropouts will be clearly documented during the trial.

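### The named observer of adverse events is the unblinded acupuncturist, and the session-linked recording does not show how safety is assessed after week 4

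*Protocol article*

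**What the plan says.** **Who observes.** The Safety assessment section covers AEs of both kinds, those associated with acupuncture and those that are not. It says that they "will be carefully observed by the acupuncturist and documented on the adverse event sheet".

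**Who records, and when.** The same section adds: "After each session, the researchers will document AEs if happens". The Data management and quality control section says: "The initial data will be filled in case report forms (CRFs) by the responsible outcome assessor".

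**Who knows the arm.** Under Blinding: "The acupuncturists will not be blinded due to the characteristics of acupuncture". Under Randomization and allocation: "The acupuncturist will be the only one who have access to both the code and the treatment labeled with the code". By contrast, "the participants, outcome assessors, and the statisticians will be blinded to the group allocation".

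**Who assesses outcomes.** Under Secondary outcomes: "A responsible research assistant will be assigned by each hospital to complete all outcome assessments during this trial". These assistants are blinded, and their assessments fall at baseline and weeks 5, 8 and 16.

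**Over what period.** The abstract states: "Safety will be evaluated during the whole process of the trial". Table 2 lists safety among its other outcomes and likewise gives the trial as its period. Safety also stands beside efficacy in the title and in the stated objective.

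**The concern.** An observer who knows the arm may look harder for events, or ask about them differently, in one arm than in the other. Here the only role named as observer is also the only role that knows the allocation. A difference in AE counts between traditional and sham acupuncture could then partly reflect how events were sought. A similarity could hide a real difference.

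It is unavoidable that the person giving the needles is unblinded. Making that person the only named observer of AEs is a choice, and the article states it.

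The second issue is timing. Recording is described in relation to sessions, whereas the safety claim extends to week 16. The section's own examples include local hematoma and infection. Either may become apparent after a session, and after the twelfth there is no further session at which to note it.

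**Working it through.** No design calculation bears on this point: response rates, alpha, power and the 170 per arm do not enter. The check sets the sections side by side and adds one count of weeks.

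**Step 1: blinding of detection.**
- Observer of AEs: the acupuncturist (Safety assessment).
- Status of that role: unblinded (Blinding), and the only holder of both code and treatment (Randomization and allocation).
- Status claimed for the trial: participant-blinded and assessor-blinded (Study design).
- Result: the efficacy outcomes go to a blinded assistant, while AE detection goes to the unblinded role. Safety is in Table 2 and the assistant is said to complete all outcome assessments, so Secondary outcomes and Safety assessment point to different people for the same outcome.

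**Step 2: who writes the record.**
- In "will be carefully observed by the acupuncturist and documented on the adverse event sheet", the acupuncturist is the agent of observing. Who does the documenting is left open.
- The later sentence gives documenting to the researchers, without saying whether they are blinded.
- Data management has the blinded outcome assessor fill in the case report forms (CRFs).
- Result: three descriptions that need to be reconciled. The answer would not change Step 1. A blinded person who enters events that an unblinded person noticed is still working from unblinded detection.

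**Step 3: time covered by the session-linked procedure.**
- Three sessions a week for 4 weeks gives 3 × 4 = 12 sessions, matching the abstract.
- The last assessment is at week 16. Weeks after the treatment period: 16 − 4 = 12, and 12/16 = 75%.
- Result: three quarters of the period lies inside the claimed safety window but after the last point at which the text describes recording. Contacts do exist in that window, at weeks 5, 8 and 16. The individual efficacy measures are tied to those weeks in the text; safety is not.

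**Step 4: relatedness.** The section distinguishes events associated with acupuncture from other events. It does not say who decides which is which.

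**The case against.** Several stronger readings are tempting, and the article does not support them.

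- **That the acupuncturist alone records AEs.** The text also names the researchers as documenting, and the blinded assessor as filling in CRFs. The acupuncturist is moreover a role at each of six centres, not one individual. This stands: the supportable point is about observation, with recording left unclear.
- **That the acupuncturist decides relatedness.** No section says so. This stands too.
- **That AEs are collected exclusively at sessions, so that the last 12 weeks go uncovered.** The abstract and Table 2 claim coverage throughout. There are three later contacts, and the blinded assistant's remit could be read to include safety at them. Figure 1, captioned as the schedule of assessments, is not shown, and a condensed article may leave follow-up procedure to the full protocol. This largely stands. What remains is that the text does not show how the claimed coverage is achieved after week 4.
- **That the bias has a known size or direction.** The article gives no AE rates or ascertainment rates, so any inflation ratio would rest on invented inputs.

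It may also be said that the Discussion already lists unblinded acupuncturists as its first limitation. That disclosure is general and concerns performing the treatment. It does not mention AE detection, which could be partly protected.

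Finally, the acupuncturist is the person present when dizziness or a hematoma occurs, and participants' recall of brief events weeks later is weaker. This is a good reason not to replace the session record. It is no reason against adding a second source.

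**Conclusion.** The point holds as a stated design choice with an avoidable weakness. The AE comparison between arms rests on detection by the one role that knows the allocation, in a trial described as assessor-blinded and with safety as a stated aim. This does not depend on what the full protocol adds about follow-up, provided that the article's assignment of the observer is accurate.

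The timing point is narrower. The recording procedure described is linked to sessions that end at week 4, and 12 of 16 weeks (75%) come later. That is a mismatch between the procedure described and the coverage claimed. It is not evidence that events in those weeks go uncollected.

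The bias cannot be quantified, in size or direction, from the document. The primary outcome, sample size and error rates are untouched. The consequence is confined to how far a difference, or an absence of difference, in AEs can be trusted.

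**What to change.** 1. Keep the acupuncturist's session record. It is contemporaneous and the best source for immediate events.
2. At the existing week 5, 8 and 16 contacts, put the same standard AE question to every participant. Participants are blinded, so their answers do not pass through an observer who knows the arm. Self-completion, after the efficacy assessments, is preferable.
3. Have relatedness coded without sight of arm, and name the role that does it.
4. Report the between-arm AE comparison from both sources, with the participant-reported one shown separately as the blinded comparison. Read it alongside the blinding assessment already planned after the last session, since it is only as blinded as the participants are.
5. Reconcile Safety assessment with Data management and quality control on who completes the AE sheet, and state how AEs are collected after week 4.

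**Cost.** One more CRF item at three existing contacts and a few lines of text, with no added visit. Recall of transient events will be imperfect, which is why the session record stays. There is a small risk that a needle-site report hints at allocation to the assistant, who goes on to assess joint counts, strength and the interviewer-administered functional index at weeks 8 and 16. Self-completion limits that risk, and asking last protects the visit in hand.
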